### Standardisation of treatments

Patients' intra- and perioperative care will be standardized and kept identical except for the technique of hepatic transection.

Patients receive combined neuraxial and general anaesthesia. However, general anesthesia alone may be chosen, if neuraxial anesthesia is not considered safe by the executing anesthesiologist and lack of patient consent.

Following laparotomy via an extended right subcostal incision, a bilateral subcostal incision (with or without vertical midline extension or a reversed L-shaped incision from xiphoid to the tip of the twelfth right rib the abdomen is initially explored for extrahepatic disease. Intraoperative ultrasound of the liver is carried out regularly to exclude previously undetected lesions. Transection of the hepatic parenchyma is carried out under low central venous pressure (< 5 cmH_2_O). Central venous pressure (CVP) is lowered via fluid restriction and clamping of the inferior vena cava (IVC) [22]. If these prove insufficient to lower CVP to a level < 5 cmH_2_O, the Trendelenburg position and administration of nitrocompounds may be used in addition. Resections are carried out without use of hepatic inflow control (i.e. portal triad clamping). However, inflow control may be used by the surgeon, if considered necessary and will be documented as a secondary endpoint. Transfusion of PRBC within the CRUNSH Trial is standardized accoriding to the standards of care at the Department of General-, Visceral- and Transplantation and the Department of Anesthesiology, University of Heidelberg (Table 2).

**Table 2 T2:** Transfusion triggers within the CRUNSH Trial

Risk profile	Minimum hemoglobin (conversion factor 0.621)
< 40 years **no **additional risk factors **no **organ function impairment	< 5.5 g/dl or 3.4 mmol/l

≥ 40 years **no **additional risk factors **no **organ function impairment	< 6 g/dl or 3.7 mmol/l

organ function impairment	< 7 g/dl or 4.3 mmol/l

coronary artery disease with no ischemia carotid artery stenosis with no ischemia history of transient ischemic attack	< 8 g/dl or 5.0 mmol/l

coronary artery disease with ischemia e.g. troponin elevation carotid artery stenosis with ischemia history of stroke	< 10 g/dl or 6.2 mmol/l

Argon beam coagulation is applied to stop minor oozing once resection is completed and sealants may be used, if deemed necessary by the executing surgeon. After hemostasis is considered secure, easy-flow drains are placed in the subphrenic and subhepatic space and the abdomen is closed in a standardized manner.

### Trial interventions

#### Group A: Clamp-crushing technique

The transectional line is marked and the liver capsule is cauterized. The liver parenchyma is then crushed stepwise using a regular Pèan clamp. Vessels of less than 2 mm in diameter are coagulated with the irrigated bipolar forceps. The remaining vessels are clipped or ligated. The hepatic veins and the portal triad are divided using sutures or the Autosuture Endo Gia™ Universal Stapler and Endo Gia™ Universal Angulating 45 mm loading units with 2.5 mm staples (Covidien).

#### Group B: Stapler hepatectomy

The transectional line is marked and the liver capsule is cauterized. For subsequent transection of the hepatic parenchyma, the liver tissue is fractured with a vascular clamp in a stepwise fashion and subsequently divided using the Autosuture Endo Gia™ Universal Stapler and Endo Gia™ Universal Straight 60 mm loading units with 2.5 mm staples (Covidien). The hepatic veins and the portal triad are divided using the Autosuture Endo Gia™ Universal Stapler and Endo Gia™ Universal Angulating 45 mm loading units with 2.5 mm staples (Covidien).

### Trial implementation

Patients scheduled for elective hepatic resection are screened consecutively for inclusion into the trial. All patients screened for the CRUNSH Trial are documented in the screening log. Patients meeting the inclusion criteria are enrolled in the trial. Informed consent has to be obtained at least on the day prior to surgery. Study visits within the CRUNSH Trial are displayed in Table 3.

**Table 3 T3:** Flow chart of the CRUNSH Trial

	Screening	Intervention	Follow Up		
	**Visit 1** **(up to 5 days before surgery)**	**Visit 2** **(day of surgery)**	**Visit 3** **(POD 1)**	**Visit 4** **(POD 3)**	**Visit 5** **(POD 7 or day of discharge)**

**Eligibility criteria Informed consent**	·				
**Medical history**	·				
**Demographics**	·				
**Physical examination**	·				
**Laboratory tests**	·		·	·	·
**Randomization**		·			
**Trial intervention**		·			
**Intraoperative parameters**		·			
**Postoperative parameters**			·	·	·

POD, Postoperative day

### Methods against Bias

#### Randomization

Patients are screened consecutively and all eligible patients are included into the trial. In order to achieve comparable groups and ensure allocation concealment patients are randomly allocated to the study groups. A block randomisation list is generated by the Institute for Medical Biometrics and Informatics (IMBI) applying SAS (SAS™ Version 9.1., SAS Institute Inc., Cary, USA). Randomization is carried out intraoperatively in case resectability is given. Randomization is carried out using opaque and sealed envelopes that are consecutively numbered. Block randomization will be performed for each center to achieve equal group sizes per center. The details of randomization will be kept in safe and confidential. Subjects withdrawn from the trial retain their identification codes (e.g. randomization number). New subjects receive a new identification code.

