### Study objectives and endpoints

The primary objective of this trial is to show that intraoperative blood loss during elective hepatic resection can be reduced by stapler hepatectomy as compared to the clamp-crushing technique.

The primary efficacy endpoint of the CRUNSH Trial is total intraoperative blood loss [ml], which is defined as blood loss from skin incision until closure of the skin. Intraoperative blood loss is measured according to the blood collected in the suction containers. Spilling water and ascites is subtracted. Furthermore, swabs are squeezed and their content will also be sucked and added to the fluid collected in the suction containers. To obtain a more precise estimate for the individual patient patient's individual transection area will be considered as a continuous covariate multivariate analysis. The transection area will be assessed using an imprint of the resected specimen on a paper sheet with a known density of 80 mg/m^2^.

To further evaluate efficacy and safety of stapler hepatectomy compared to the clamp-crushing technique, a set of general as well as surgical variables are documented as secondary endpoints [21]. The secondary endpoints of the trial are summarized together with their definition in Table 1.

**Table 1 T1:** Secondary endpoints of the CRUNSH Trial

Secondary endpoint	Definition and assessment of outcomes
*Blood loss during liver transection [mL]*	Blood loss from beginning of parenchymal transection until minor oozing is stopped. To assess blood loss during liver transection the suction device will be connected to a new suction container for the period of actual hepatic transection.
Blood transfusion:	Administration of blood transfusions is documented for the intraoperative and postoperative period until 48 hours postoperatively. Documentation includes number of patients who received blood transfusions as well as amount of transfused packed red blood cells (PRBC) [units].
Operation time [min]:	Time from skin incision to placement of last skin staple/suture.
Liver transection time [min]:	Time from beginning to end of liver transection.
Duration of postoperative hospital stay [days]:	Time from day of operation to day of discharge.
Duration of ICU stay [days]:	Time on the Intensive Care Unit (ICU). Patients' stay in the recovery room and Intermediate Care (IMC) unit exceeding 24 hours is considered as ICU stay.

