#### Blinding

Patients are blinded for the study intervention. Blinding of the surgeon and people in the operating room is not feasible. Therefore a third party blinded to patients' allocated treatment group assesses postoperative outcomes.

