### Sample size

The sample size is based on the primary outcome parameter and the primary analysis. Internal observations (Department of Surgery, University of Heidelberg) showed a mean intraoperative blood loss of 700 ml for patients undergoing stapler hepatectomy with a sample standard deviation of about 550 ml [19]. To detect a clinically relevant absolute difference reduction in intraabdominal blood loss of 280 ml with significance α = 5% and a power of (1-β) = 80% n = 122 patients have to be randomized in the study (n = 61 patients per group) using two-sided t-test. Considering an estimated intraoperative drop-out rate of about 10% (e.g. unexpected death prior to beginning of transection, protocol violations) eight additional patients will be randomized and the total sample size accounts for n = 130 patients (n = 65 patients per group).

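### Randomisation is tied only to resectability, leaving an interval before transection in which an unblinded team knows the arm, blood loss counts in the primary endpoint and patients can be lost

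*Protocol article*

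**What the plan says.** All references are to the protocol article.

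- **Randomization:** "Randomization is carried out intraoperatively in case resectability is given". No other condition on the moment of opening is stated.
- **Standardisation of treatments:** exploration for extrahepatic disease and intraoperative ultrasound are described first, then transection under low CVP. Randomisation is not placed in this sequence.
- **Sample size:** the examples given for intraoperative drop-out are "unexpected death prior to beginning of transection, protocol violations". To cover drop-out, "eight additional patients will be randomized and the total sample size accounts for n = 130 patients".
- **Blinding:** "Blinding of the surgeon and people in the operating room is not feasible". The remedy is that "a third party blinded to patients' allocated treatment group assesses postoperative outcomes".
- **Study objectives and endpoints:** the primary endpoint is "blood loss from skin incision until closure of the skin". Blood loss during transection alone is collected in a separate container, as a secondary endpoint (Table 1).
- **Statistical analysis:** the confirmatory ANCOVA includes all patients as randomised, with resection area and CVP during transection as covariates.
- **Trial interventions:** both groups begin with the same marking of the line and cautery of the capsule. They differ in how the parenchyma is divided. They also differ in how the hepatic veins and portal triad are divided: sutures or stapler in group A, stapler in group B.

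**The concern.** In a trial whose operating team cannot be blinded, the allocation is best disclosed as late as the comparison permits. Everything done between disclosure and the first step that differs by arm can be influenced by knowledge of the arm without being part of the technique under test. Two things are at stake.

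1. **Bias in the primary endpoint.** Blood lost before the envelope is opened cannot depend on the arm and only adds noise. Blood lost after opening but before the techniques diverge can depend on it, and it is counted. The blinded third party assesses postoperative outcomes, so that safeguard does not reach intraoperative blood loss.
2. **Losses that say nothing about the technique.** A patient randomised but lost before transection has no resection area and no CVP during transection. An ANCOVA on complete cases would drop that patient, contrary to the stated analysis of all patients as randomised. Keeping the patient requires a rule for the missing covariates and dilutes the contrast.

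**Working it through.** **Does the interval exist?** The allocation rule names resectability and nothing later. The drop-out allowance gives death before the start of transection as an example and adds randomised patients to cover it. A randomised patient can be lost before transection only if randomisation comes before it. The interval therefore follows from the protocol's own text.

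**Which blood loss is affected?** Split the operation into four parts:
- (a) incision to envelope opening: counted, independent of arm;
- (b) opening to start of transection: counted, arm known;
- (c) transection until oozing stops: counted, and also measured separately;
- (d) afterwards until skin closure: counted, arm known.

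Total minus the transection container gives (a) + (b) + (d). Part (b) cannot be isolated from the planned measurements without a suction reading at opening.

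**Is early disclosure needed?** The first steps in both arms are identical (marking, capsule cautery). The first difference is parenchymal division, or vessel division if that comes earlier. The article does not state that order, and it gives no reason to disclose before whichever of the two comes first.

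**The plan's sample size.** Inputs (Sample size section): difference 280 ml, SD 550 ml, two-sided alpha 5%, power 80%.

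n per arm = 2 × (1.960 + 0.842)² × 550² / 280² = 60.6, rounded up to 61, so 122 in total. This reproduces the stated figure (the exact t-test gives 61.5 per arm). With eight more patients: 122 + 8 = 130, or 65 per arm.

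**Illustration of dilution.** Assume that a share d of randomised patients never reach transection, stay in the analysis, show no treatment effect and have the same SD. The difference becomes 280 × (1 − d). With standard error 550 × √(2/65) = 96.5 ml, power = Φ(280(1 − d)/96.5 − 1.96).

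| d (assumed) | Difference, ml | Power at 65 per arm | n per arm for 80% power |
|---|---|---|---|
| 0% | 280 | 82.7% | 61 |
| 2% | 274.4 | 81.2% | 64 |
| 5% | 266 | 78.7% | 68 |
| 10% | 252 | 74.3% | 75 |

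The 10% row is an extreme: it treats the whole drop-out allowance as loss before transection, whereas the article also puts protocol violations in it. No value of d is given.

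**Size of the bias.** The article gives no blood loss for part (b) and no estimate of how knowledge of the arm would alter it. No calculation is possible.

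**The case against.** The strongest case against the point is that the wording states a condition, not a clock time. It is compatible with opening the envelope just before transection, and a condensed article may leave the exact moment to the full protocol. Care is standardised and identical apart from the technique, the analysis is by intention to treat, and blood loss during transection is measured separately. The team also remains unblinded through transection and closure, so later opening removes only part of the exposure.

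Much of this stands. Practice may already be later than the text requires, and the sentence would then only record it. But the drop-out example shows that losses between allocation and transection are expected, so the matter is not purely one of omitted detail. Standardisation lessens the risk without removing it: further measures to lower CVP and the use of inflow control are left to judgement. The CVP limit itself is given in cmH2O under Standardisation of treatments and in mmHg under Standardization of care, and these must be reconciled.

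Several stronger readings are tempting but not supported:
- *That preparation of the liver, fluid restriction and CVP lowering take place in the interval.* The article does not say which steps fall there; this is inference.
- *That 10% of 130, or 13 patients, would be lost and that all such losses are avoidable.* The 10% covers more than losses before transection, only eight patients are added, and a shorter interval can remain after the change, notably where an arm-specific vessel division comes first.
- *That the shift in blood loss can be put in millilitres or as a share of the 280 ml target.* No passage gives a basis for a size or a direction.
- *That later opening makes the CVP covariate a baseline value.* The planned covariate is CVP during transection, which is measured after randomisation under either timing.

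**Conclusion.** The point holds as a design weakness that should be corrected, with medium confidence. The stated rule ties allocation only to resectability, and the protocol itself expects losses between allocation and transection. In that interval an unblinded team accrues blood loss that counts in the primary endpoint, and patients lost there lack both ANCOVA covariates.

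The size of any bias is unknown. The power figures are conditional on an assumed share of patients not reaching transection: a loss of 1.5 points at 2% (82.7% to 81.2%) and of 4.0 points at 5% (82.7% to 78.7%). They show that small shares cost little power, so the case for change rests mainly on closing an avoidable route to bias at almost no cost. It does not rest on evidence that the result would be materially wrong.

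**What to change.** Amend the Randomization section along these lines:

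> The envelope is opened only after resectability has been confirmed and preparation common to both arms is complete, immediately before the first step that differs by arm: parenchymal transection, or an arm-specific vessel division if that comes earlier. The clock time and the suction-container reading are recorded at opening.

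The reading lets blood lost before allocation be separated from blood lost after it. The change leaves the treatments, the primary endpoint and the sample size as they are. Its cost is one sentence and two recorded items. The small downside is that the team learns the allocation later in the operation and must have both instrument sets ready.

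The change reduces arm-aware preparation and losses before transection but does not eliminate them. Any randomised patient who still does not reach transection will need a rule for the missing covariates, which can sit in the statistical analysis plan. CVP during transection remains a post-randomisation covariate and has to be considered separately.

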#### Blinding

Patients are blinded for the study intervention. Blinding of the surgeon and people in the operating room is not feasible. Therefore a third party blinded to patients' allocated treatment group assesses postoperative outcomes.

#### Standardization of care

To assure comparable treatment of patients, all surgeons who participate in this trial, will be instructed on both study interventions. Intra-and perioperative care is standardized. In particular, central venous pressure (CVP) will be lowered to < 5 mmHg for the period of parenchymal transection and resections in both study arms will be performed without routine use of the vascular control. Furthermore, the area of resection will be included in the multivariate analysis as a continuous covariate.

### Sample size

The sample size is based on the primary outcome parameter and the primary analysis. Internal observations (Department of Surgery, University of Heidelberg) showed a mean intraoperative blood loss of 700 ml for patients undergoing stapler hepatectomy with a sample standard deviation of about 550 ml [19]. To detect a clinically relevant absolute difference reduction in intraabdominal blood loss of 280 ml with significance α = 5% and a power of (1-β) = 80% n = 122 patients have to be randomized in the study (n = 61 patients per group) using two-sided t-test. Considering an estimated intraoperative drop-out rate of about 10% (e.g. unexpected death prior to beginning of transection, protocol violations) eight additional patients will be randomized and the total sample size accounts for n = 130 patients (n = 65 patients per group).

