### Statistical analysis

Statistical methods are used to assess the quality of data, homogeneity of treatment groups, endpoints and safety of the two intervention groups. The confirmatory analysis is performed on the basis of an intention-to-treat (ITT) population and with respect to ITT principles.

Categorical data are summarized by means of absolute and relative frequencies (count and percent). Continuous data are presented by means of the following summary statistics: the number of observations, median, minimum, median and maximum. Wherever appropriate, data are visualized by box-whisker plots or histograms. The primary efficacy endpoint is amount of total intraoperative blood loss. The underlying two-sided null-hypothesis is that both study interventions lead to similar intraoperative blood loss:

$${\text{H}}_{0}:\mu 1-\mu 2=0$$

The alternative is that one intervention performs better than the other:

$${\text{H}}_{1}:\mu 1-\mu 2\neq 0$$

A confirmatory intention-to-treat analysis (2-sided test), including all patients as randomized, is performed on the amount of intraoperative blood loss between the two groups. Analysis of covariance (ANCOVA) is used to detect possible treatment differences with intraoperative blood loss as dependent variable, area of resection and CVP during transection as continuous covariates and type of intervention as factor. The sample size calculation is based on a two-sided t-test, and it can be assumed that evaluation with analysis of covariance has the same or even higher power.

Secondary endpoints will be analyzed in an exploratory way, using appropriate statistical methods based on the underlying distribution of the data. All analysis will employ SASα Version 9.1.

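### Eight extra patients cover about 6% drop-out, not the stated 10%, and the allowance counts as lost the protocol violators whom the intention-to-treat analysis keeps

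*Protocol article*

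**What the plan says.** The Sample size section of the protocol article plans to detect a "reduction in intraabdominal blood loss of 280 ml" with a "sample standard deviation of about 550 ml", at 5% significance and 80% power, "using two-sided t-test". This gives 122 patients, 61 per group. The allowance that follows reads "estimated intraoperative drop-out rate of about 10% (e.g. unexpected death prior to beginning of transection, protocol violations) eight additional patients", and the total becomes 130, 65 per group.

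The Statistical analysis section defines who is analysed: "A confirmatory intention-to-treat analysis (2-sided test), including all patients as randomized, is performed". The model is an ANCOVA with resection area and central venous pressure as covariates. The section assumes, without a figure, that its power is at least that of the t-test.

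**The concern.** Two things in the allowance do not fit.

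- **The arithmetic.** The total of 130 is presented as the result of a 10% allowance on 122, but eight patients are too few for that rate. Sample size, drop-out rate and t-test power cannot all stand as written.
- **The definition.** Protocol violations are given as an example of drop-out. Under the stated analysis rule a violator is not lost: he or she is analysed in the allocated arm. Loss reduces the number analysed, while retention may shrink the observed difference. These act on power differently, and an allowance for loss does not provide for dilution.

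At stake are the accuracy of the published power statement and consistency about who enters the primary analysis. The surgeon is not blinded (Blinding section) and the endpoint is intraoperative blood loss, so nothing in the planning text should leave room to set violators aside.

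**Working it through.** **Inputs**, all from the Sample size section: difference 280 ml, SD 550 ml, two-sided 5%, power 80%, 1:1 allocation, drop-out about 10%, eight patients added.

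**1. Base number.** Normal approximation, per group: 2 × (1.960 + 0.842)² × 550² / 280² = 60.6, so 61, and 122 in total. The plan's figure reproduces. The exact t calculation gives 61.5, so 62 per group, a trivial difference.

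**2. Inflation for drop-out.**
- N/(1 − d): 122/0.9 = 135.6, so 136 (68 per group).
- N × (1 + d): 122 × 1.1 = 134.2, so 135.
- What eight patients cover: 8/130 = 6.2% (or 8/122 = 6.6%).

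Neither convention gives 130.

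**3. Power if patients are lost** (difference 280 ml, SD 550 ml):

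| Analysed | Per group | Normal approximation | Exact t |
|---|---|---|---|
| 130 (none lost) | 65 | 82.7% | 82.1% |
| 122 (6.2% lost) | 61 | 80.3% | 79.6% |
| 117 (10% lost, 130 × 0.9) | 58.5 | 78.6% | 77.9% |

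Like for like, 117 instead of 122 costs 1.7 points on either method.

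**4. Possible ANCOVA gain.** If the covariates correlate with the outcome at r, the residual SD is 550 × √(1 − r²). The protocol gives no r, so these values are assumptions. With 117 analysed, exact t:
- r = 0.1: 78.3%
- r = 0.2: 79.6%
- r = 0.3: 81.7%

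**5. Power if violators are kept.** Suppose all 130 are analysed and a fraction f contributes no difference between techniques. The mean effect is then 280 × (1 − f). The protocol gives no f, so this is an assumed range (exact t, 65 per group):

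| f | Effect (ml) | Power |
|---|---|---|
| 0 | 280 | 82.1% |
| 2% | 274.4 | 80.6% |
| 5% | 266 | 78.1% |
| 10% | 252 | 73.6% |

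Interpolating between 2% and 5%, power reaches 80% at f of about 2.7%, which is 0.027 × 130 = 3.5 patients.

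**6. A mixture.** Suppose half of the 10% are lost and half are kept with no effect. Then 130 × 0.95 = 123.5 are analysed, the effect is 280 × (1 − 0.05/0.95) = 265.3 ml, and power is 75.8%. The 77.9% in step 3 and the 73.6% in step 5 are therefore the two ends of one range and must not be added together.

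**The case against.** The strongest reply is that little power is at risk. The 122 comes from the normal approximation, and by exact t it already gives 79.6%, so a full 10% loss costs under 2 points. The primary analysis is an ANCOVA, and a modest correlation could recover that. Keeping violators also means that fewer patients are lost: with all 130 analysed and no dilution, power is above 80%. All of this stands. It limits the consequence but does not make 130 the answer to a 10% allowance.

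Three stronger readings are tempting, and the documents do not support them.

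- **That 80% power is not delivered.** A reader might infer this from 77.9% or 73.6%. The first leaves out the unquantified ANCOVA gain. The second assumes that the whole 10% are violators with no technique difference, although the protocol also names death before transection and gives no split.
- **That violators will be excluded from the primary analysis.** The Statistical analysis section invokes intention-to-treat twice and includes everyone as randomised. No section says that violators are removed. The conflict lies in the planning allowance; the analysis rule is clear.
- **That randomised patients are replaced.** The Randomization section says "New subjects receive a new identification code", next to a rule that withdrawn subjects keep theirs. This governs how codes are handled and does not state replacement.

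**Conclusion.** The point holds as a correction of a stated figure and a definition. It is not a demonstrated failure of power.

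- The number 130 does not follow from 122 and 10%. It covers about 6%; 10% needs 136. This rests only on the protocol's own inputs.
- With 130 randomised and 10% truly lost, t-test power is about 78%, assuming the planned difference and SD and no ANCOVA gain.
- The drop-out definition does not match the analysis population. With violators retained, power runs from 82.1% undiluted to 73.6% in the assumed worst case, crossing 80% at about 2.7% dilution. Where the trial falls in that range cannot be told from the document.

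The sample size, the primary endpoint and the primary analysis can stay as they are.

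**What to change.** In the Sample size section, keep n = 130 and make one of two statements:
- 130 patients cover a drop-out of about 6%; or
- with 10% drop-out, 117 patients are evaluable and t-test power is about 78%, before any gain from covariate adjustment.

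In the same section, define drop-outs as randomised patients without a measurable primary outcome, and take protocol violations out of the examples. Add that violators remain in their allocated arm in the confirmatory analysis, so that their effect on power is dilution of the assumed difference and not loss of patients.

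The cost is wording only, with no additional patients; the second option states a slightly less favourable power. Holding to both 10% drop-out and 80% t-test power would instead mean randomising 136, six more than planned, which this correction does not require.
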